## Abstract

**Background::**

Focus and concentration are influenced by various environmental factors, such as listening to music. Recent research highlights the individualized nature of music’s effects on concentration, as responses vary significantly between individuals based on music genres and personal preference. Traditional population-based studies often obscure these between-person differences, while N-of-1 trials, which are individual crossover trials, can provide a personalized approach by allowing each participant to serve as their own control. This study design is particularly suited for examining how self-selected music genres might enhance or alter concentration in each individual. By leveraging an N-of-1 trial design, this study aims to contribute to the growing body of research investigating personalized cognitive interventions, providing insights into individual effects and variations in response to music.

**Methods::**

The study will include approximately 23 participants, who will be allocated to a block-randomized sequence with two cycles, each consisting of 3-min periods of listening to music (intervention, A) and 3 min of no music (control, B) in random order. Study participants will select one of fourteen predefined music genres, with or without lyrics, as their intervention. A playlist with preselected songs from this genre will be played and compared to not listening to music. To minimize the effects of carryover and concentration loss during the study, a 1-min break is planned between each period, resulting in a total duration of around 15 min. Concentration will be assessed by the number of correct classifications of a digital version of the Stroop test within each period. After each period, a short questionnaire will be administered to collect self-assessed concentration and stress scores. Additionally, physiological biomarkers will be assessed using wearables such as Electroencephalography, Heart Rate Variability, Electrodermal Activity, and eye- and pupil-movement data. In the statistical analysis, Bayesian generalized linear mixed models will be used to estimate the intervention effects of music on correct answers of the Stroop task on the individual level and population level.

**Discussion::**

This study will provide insights into the personalized effects of music on concentration, providing a blueprint for individuals on how they may test and improve their concentration.

## Introduction

1

The impact of music on cognitive performance, particularly on concentration and attention, has been a focal point of research in psychology and neuroscience. In 1976, Parente investigated the performance of the Stroop task in conditions (1) listening to preferred music, (2) least preferred music, and (3) control (no music), resulting in better performances of no music and preferred music compared to least preferred music [1]. These results were not fully aligned with a previous study, where noise was reducing the time for the Stroop task [2], when assuming music is defined as a form of noise [3].

The so-called *Mozart effect*, a phenomenon suggesting that listening to Mozart’s compositions can improve spatial task performance, was first investigated in 1993 by Rauscher et al. [4]. In this study, the performance of three sets of standard IQ spatial reasoning tasks was compared among 36 study participants under 3 conditions: (1) listening to Mozart’s *Sonata for two pianos in D major, K488*; (2) listening to a relaxation tape; and (3) silence. No personal preferences were considered in this study. However, subsequent studies, including those by Steele et al. have failed to replicate the results, calling into question the robustness of the Mozart effect and suggesting that the influence of music on concentration may be more nuanced than previously thought [5]. Other studies have investigated the relationship between arousal and mood and their impact on performance in spatial tasks, while the Mozart effect was considered an artifact of this relationship [6], [7].

Following that, a range of studies have examined how people react differently to music [8], [9], [10]. In 1997, Furnham and Bradley [8] compared the effects of being exposed to background pop music or silence in introverts and extroverts on different tasks, such as memory tasks and reading comprehension. They showed that introverts tend to perform worse under music conditions, especially in a memory task after 6 min. In 2002, Furnham and Strbac [9] compared silence with predefined unreleased Garage-style songs and noise. They found a better overall performance under silence compared to music and noise. In a reading comprehension task, they identified a performance difference between introverts and extroverts in the music and noise conditions. In contrast, in a prose recall task and a mental arithmetic task, they did not identify a difference [9]. Cassidy et al. compared the effect of listening to high arousal music, low arousal music, noise, and silence in introverted and extroverted individuals. Their results indicated that introverts were performing better on immediate recall, free recall, and delayed recall tasks, while there were no differences with respect to a Stroop task [11]. Besides studies of personality, Wu and Shih showed that background music could improve the attention performance of musicians more compared to non-musicians [10]. In 2025, Clark and Leal investigated the effect of prominent music on learning behavior. Based on their study, they suggested that music interventions do not uniformly impact memory and need to be personalized [12].

For investigation of the association between personality traits and music genres, using a classification model for music genres can be helpful. Rentfrow proposed a five-factor model called MUSIC, how music can be classified into (1) a mellow factor (smooth and relaxing), (2) an unpretentious factor (sincere and rootsy), (3) a sophisticated factor (classical, operatic, world, jazz), (4) an intense factor (loud, forceful, energetic), and (5) a contemporary factor (rhythmic, percussive) [13]. Greenberg associated those music factors with personality using the empathizing-systemizing theory [14]. Similar studies have used music classification to associate listening behaviors and emotions [15], [16], [17].

The specific characteristics of music that induce relaxation have been examined in experimental contexts. For example, research by Shepherd et al. compared silence, aircraft noise, and different music genres, including monaural beats at specific frequencies, to a composition called *Weightless*, purportedly designed to be ”the most relaxing song in the world” [18]. Their findings suggest that structured, low-tempo music lowering arousal levels may be more effective compared to silence or certain environmental noises [18]. Lui and Grunberg employed skin conductance to assess how music versus silence affects arousal, concluding that silence can be as influential as music in managing arousal levels during stressful interactions [19]. Shih et al. investigated the effect of background music without lyrics on attention performance measured through Chu’s attention test within a randomized controlled trial [20]. In another study, Huang and Shih showed that background music influences workers’ attention: performance was dependent on the listener’s fondness rather than the type of music [21]. Souza and Barbosa investigated whether there is an effect-difference between music with and without lyrics. In their study, music with lyrics hindered verbal memory, visual memory, and reading comprehension; music without lyrics, such as hip-hop or Lo-Fi, did not show a significant effect [22].

In the medical context, music therapy has gained more popularity over the last decade, such as for anxiety and pain [23]. A variety of studies have explored the nuanced effects of music on stress and anxiety, with findings suggesting that different genres and tempos yield varying outcomes [24], [25], [26]. For instance, Labbé et al. examined different types of music and their effects on stress, anxiety, and anger, finding that particular types of music can serve as effective coping mechanisms for stress reduction depending on the listener’s pre-listening mental state [24]. Further supporting this, a randomized controlled trial by Lee et al. found that music therapy significantly influenced the cardiovascular and autonomic nervous systems in stress-induced university students, highlighting physiological changes that contribute to stress reduction and enhanced well-being [25].

From a neurophysiological perspective, music has been shown to modulate brain activity associated with attention, cognitive control, and emotional processing. Electroencephalography (EEG) studies indicated that listening to music can alter cortical oscillatory patterns, such as frontal theta and alpha activity, which have been linked to attentional engagement and cognitive workload [27], [28], [29]. Furthermore, music has been reported to influence autonomic nervous system activity, reflected in physiological measures such as Heart Rate Variability (HRV) and Electrodermal Activity (EDA), which are sensitive to changes in arousal, stress, and task engagement [30], [31]. These research studies have varied from investigating the overall effect of listening to a specified music genre on concentration, the individual response based on personal characteristics or music preferences, to the effect on different emotions based on the music characteristics.

In our study, we aim to investigate the effect of music from a self-selected music genre on individuals’ concentration, particularly when focusing on attention-based tasks. By collecting baseline data about personality, music preferences, and listening fondness as well as physiological sensor data, we will further explore diverse interactions of music.

### Objectives

1.1

This study investigates the effect of music on concentration through a rigorous experimental design, assessing individual changes in attention levels. By including various music genres chosen by the study participants, this study will contribute to understanding the role of music in cognitive performance, ultimately providing insights into whether and potentially how music can enhance concentration.

The study addresses one primary and two secondary research questions.

•*Primary research question:* Does listening to music from a self-selected genre influence cognitive task performance compared with a no-music condition, on average on the population level and for how many individual participants?

Secondary research questions:

1.To what extent can physiological sensor data (e.g., Electroencephalography (EEG), Heart Rate Variability (HRV), Electrodermal Activity (EDA), Eye Tracking) serve as proxies for concentration changes, as measured by the cognitive task?2.To what extent do between-person differences in intervention effects on cognitive task performance be explained by effect modifiers (e.g., music preference, baseline characteristics, physiological traits)?

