#### Sample size

We estimated the required sample size (i.e., number of participants) for testing a population-level average difference in the primary outcome (Stroop test, see Section 2.3) between periods of intervention condition (self-selected music) and control condition (no-music) through simulation studies. The simulation was performed in R using lme4, with seed 123 for reproducibility. We assumed a correct answer rate of 95% in the no-music condition and 96% across all self-selected music conditions based on pilot testing of the digital version of the Stroop task. That is, we assumed a difference in correct answer rate between the conditions of 1%. We assumed 150 observations per 180-second period based on an average response rate of 1.2 s per answer. This yielded about 600 observations per participant across all four periods. Corresponding to those values, we simulated data of our binary outcome variable $Y_{ij}$ (0 = incorrect response, 1 = correct response) for patient i at time point j (subsequently numbered throughout all periods) with a generalized linear mixed model (GLMM) using an intercept of $\beta_{0}$, a fixed effect $\beta_{1}$ of treatment $A_{ij}$ (0 = control condition, 1 = intervention) and we assumed a random effect $u_{i}∼N\left(0,\sigma_{u}^{2}=0.05\right)$ for each individual: (1)$$\beta_{0}=\mathrm{logit}\left(0.95\right)$$$$\beta_{1}=\mathrm{logit}\left(0.96\right)-\mathrm{logit}\left(0.95\right)$$$$p_{ij}={\mathrm{logit}}^{-1}\left(\beta_{0}+\beta_{1}\cdot A_{ij}+u_{i}\right)$$$$y_{ij}=\text{Bernoulli}\left(p_{ij}\right)$$

We simulated 5000 series of N-of-1 trials for each of the following number n of participants: n∈[15,16,…,29,30]. We used a fixed treatment effect $\beta_{1}$, random effect $u_{i}$, and the outcome was randomly drawn from a Bernoulli distribution as shown in Eq. (1). The seed was set to ‘123’.

Next, for each n, we analyzed each of the 5000 series of N-of-1 trials using the generalized linear mixed model (GLMM) defined in Section 2.5. For each n, we estimated the power as the ratio of p-values of the Wald z-test for $\beta_{1}$ that were <0.05 across the 5000 series of trials and calculated the 95% confidence interval for the estimated power based on the Monte Carlo error of the estimated power: (2)$${\text{CI}}_{\text{upper}/\text{lower}}=\text{Power}\pm 1.96\cdot \sqrt{\frac{\text{Power}\cdot \left(1-\text{Power}\right)}{5000}}$$

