#### Primary analysis

To estimate the population-level estimand of interest, we will use a Bayesian generalized linear mixed model (GLMM). The model will include a fixed effect for condition (music vs. no music) and a participant-specific random intercept to account for baseline differences in performance. Hence, it will account for the repeated binary outcomes within participants and individual differences in baseline performance. We will use weakly informative priors to regularize estimates and make prior assumptions explicit. The posterior distribution of intervention effect will be summarized by posterior means/medians, 95% credible intervals, and posterior probabilities (e.g., $\mathrm{Pr}\left(\beta_{1}>0|\text{data}\right)$). Marginal risk differences and odds ratios will be derived from posterior predictive simulations to facilitate interpretation on both the probability and odds scales.

More formally, let $y_{ij}=1$ denote the correct answer in the Stroop task j for individual i and $y_{ij}=0$ denote a wrong answer, respectively. This will be drawn from a Bernoulli distribution with the corresponding probability $p_{ij}$: (3)$$y_{ij}∼\text{Bernoulli}\left(p_{ij}\right)$$

We will use a logistic link, and a fixed effect for the condition $A_{ij}$, where $A_{ij}=1$ denotes listening to music and $A_{ij}=0$ denotes not listening to music, respectively. Further, we will include a random intercept $b_{i}∼N\left(0,\sigma_{b}^{2}\right)$ for each participant i drawn from a normal distribution. (4)$$\text{logit}\left(p_{ij}\right)=\beta_{0}+\beta_{1}\cdot {\text{A}}_{ij}+b_{i}$$

We will use non-informative Priors for the β coefficients following a normal distribution and for $\sigma_{b}^{2}$ a half-student-t distribution with a degree of freedom of 3 and a standard deviation of 1. For the intercept $\beta_{0}$, we choose a large standard deviation to allow a high flexibility: (5)$$\beta_{0}∼N\left(0,5^{2}\right)$$$$\beta_{1}∼N\left(0,1\right)$$$$\sigma_{b}^{2}∼\text{Half-student-t}\left(v=3,\sigma^{2}=1\right)$$

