To assess the robustness of the findings, sensitivity analyses are planned. First, as a non-parametric robustness check, we will perform Fisher’s exact test on aggregated counts of correct versus incorrect responses under music and no-music conditions, which provides a simple benchmark for differences between music and no-music conditions, assuming independence of observations. Next, we will include chronological time in the Bayesian generalized linear mixed model (GLMM) with uninformative priors ($\beta_{i}∼N\left(0,1\right)$), as a proxy for time-varying effects of factors such as fatigue or learning. From the fitted models, we will report odds ratios with 95% credible intervals and compute average marginal risk differences for interoperability.

If a value of $y_{ij}$ is missing (e.g., the participant did not respond within the given time frame), it will count as incorrect and be coded as 0. In the case that multiple consecutive values are missing, the length of the missing data will be reported.

In addition to the population-level estimates, we will estimate individual-level intervention effects by contrasting within-person differences in accuracy between music and no-music conditions for each participant across their trial periods. To illustrate this, we will follow the Independent Bayes Approach (IBA) described in Hoffmann et al. [41], presenting participant-specific estimates, visualizations, and posterior probabilities of benefit where appropriate. These analyses will help to characterize heterogeneity in individual responses to the intervention. For the analysis, we will use aggregated counts of the correct answers of the Stroop task.

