#### Secondary analysis

To address the first secondary question, to what extent physiological sensor data can serve as proxies for concentration changes, as measured by the cognitive task, we will use descriptive and visual analytics. Time-series plots, condition-wise summaries, and participant-level comparisons will be generated to explore signal patterns across the intervention and control phases. If sensor data is missing, we will not impute the data and report only cases where we observe the sensor data for at least 60 consecutive seconds in every period. Summary statistics such as means, standard deviations, medians, and interquartile ranges will be computed for each physiological signal, stratified by condition (music vs. no music) and participant. Visualizations may include line plots, box plots, and heat maps to explore temporal dynamics and individual differences. Furthermore, methods from time series analysis will be applied to detect changes before and after incorrect answers, thereby elaborating on the stress and concentration levels in relation to the given answer within this time frame.

To explore the second secondary research question, the extent to which individual differences such as music preference or playing an instrument moderate the effect of music on cognitive task performance, we will first stratify the descriptive statistics described in Section 2.5 for different subgroups. Subgroup analyses will be conducted only for groups that include at least five participants meeting the specific criteria. First, we will investigate listening behavior and music preferences. For this analysis, we will distinguish between participants who often or always listen to music at work and those who listen only occasionally, rarely, or never. Next, we will investigate the subgroup of participants who have ever played an instrument (Answers *Yes* and *Not anymore*). Finally, we will include these variables of interest with uninformative priors (β∼N(0,1)) as interaction effects in the Bayesian generalized linear mixed model (GLMM) used for the primary research question. We will adjust the model for the individual characteristics and experience and report the estimated effect and its estimated 95% credible interval for each model.

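### The model planned for secondary question 2 has no term for unexplained between-person differences in the music effect, so it cannot show how much the modifiers explain, and its interaction intervals are too narrow if such differences exist

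*Protocol article*

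**What the plan says.** Objectives, secondary question 2: "To what extent do between-person differences in intervention effects on cognitive task performance be explained by effect modifiers".

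Secondary analysis (section 2.5) sets out two steps for this question:
- Descriptives: "we will first stratify the descriptive statistics described in Section 2.5 for different subgroups", limited to groups of at least five participants.
- Modelling: the modifiers enter "as interaction effects in the Bayesian generalized linear mixed model (GLMM) used for the primary research question", and the team will "report the estimated effect and its estimated 95% credible interval for each model".

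Primary analysis (section 2.5) fixes the model to which the interactions are added: "The model will include a fixed effect for condition (music vs. no music) and a participant-specific random intercept". Eq. (4) confirms this, with one common β1 for music and a random intercept b_i. No random effect multiplies the condition.

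The Primary analysis also plans separate participant-by-participant Bayesian estimates and says of them: "These analyses will help to characterize heterogeneity in individual responses to the intervention". The protocol does not link these estimates to the modifiers.

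**The concern.** The question asks how far the modifiers account for differences between people in the music effect. An answer needs two components: the differences that the modifiers carry, and the differences that remain once they are in the model. The planned model has only the first. An interaction coefficient gives the size of the contrast between, say, people who have played an instrument and people who have not. It does not say whether that contrast is most of the person-to-person variation or a small part of it.

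The same omission affects the intervals. The modifiers are properties of people, so the information on an interaction is limited by the number of people in each group. If people within a group truly differ in their response to music, a model that denies this treats the roughly 600 responses per person as if they settled the group contrast. A credible interval that excludes zero could then be reported as evidence about who benefits when it reflects which people happened to be in each group. The protocol itself expects responses to vary between individuals; that is its reason for using an N-of-1 design.

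**Working it through.** **Structure.** Add a modifier x_i to Eq. (4):

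logit(p_ij) = β0 + β1·A_ij + δ·x_i + γ·A_ij·x_i + b_i

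The music log odds ratio for person i is β1 + γ·x_i. Its between-person variance is γ²·Var(x), with no residual term. With a participant-specific effect s_i ~ N(0, σ_s²) it would be γ²·Var(x) + σ_s². The planned model is the case σ_s = 0, fixed in advance and not estimated.

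**Inputs from the protocol** (Sample size): "We assumed a correct answer rate of 95% in the no-music condition and 96% across all self-selected music conditions"; 150 responses per period, so 300 per condition per person; 23 participants.

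**Assumed, because the protocol gives no values:** a binary modifier split 11/12; σ_s of 0.2, 0.3 or 0.5 on the log-odds scale; where needed, γ = 0.3. For scale, the planned average effect is β1 = logit(0.96) − logit(0.95) = 0.234.

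**Step 1: the plan's own figure.** The protocol states no figure for question 2, so the population-level power serves to check the inputs.
- Sampling variance of one person's log odds ratio (at b_i = 0): 1/(300·0.95·0.05) + 1/(300·0.96·0.04) = 1/14.25 + 1/11.52 = 0.157, so SE 0.396.
- SE of β1 with 23 people: 0.396/√23 = 0.0826.
- Power: Φ(0.234/0.0826 − 1.96) = Φ(0.87) ≈ 81%. The protocol states 81.3% (95% CI 80.2%–82.4%). The inputs reproduce it. That simulation also gave everyone the same music effect.

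**Step 2: one coefficient fits very different answers.** With γ = 0.3 and an 11/12 split, the explained variance is 0.3²·(11/23)·(12/23) = 0.0225. Explained share = 0.0225/(0.0225 + σ_s²):

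| σ_s | true explained share |
|---|---|
| 0.2 | 36% |
| 0.3 | 20% |
| 0.5 | 8% |

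The planned model has no parameter that distinguishes these rows.

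**Step 3: interval width.** Take γ = 0.
- SE that the planned model works with: √[0.157·(1/11 + 1/12)] = √(0.157·0.174) = 0.165.
- Actual SD of the estimate: √[(0.157 + σ_s²)·0.174].
- Chance that a nominal 95% interval excludes zero: 2·Φ(−1.96·0.165/actual SD).

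| σ_s | actual SD | ratio to 0.165 | excludes zero, formula | excludes zero, simulation |
|---|---|---|---|---|
| 0 | 0.165 | 1.00 | 5% | 5–6% |
| 0.2 | 0.185 | 1.12 | 8% | 7–9% |
| 0.3 | 0.207 | 1.25 | 12% | 12–16% |
| 0.5 | 0.266 | 1.61 | 22% | 25–27% |

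The simulation column is the range over repeated simulations of 23-person trials, with random-intercept variance 0.05 and the random-intercept model fitted by maximum likelihood. The planned N(0,1) prior on γ changes little: it shrinks the estimate by a factor of about 1/(1 + 0.165²) = 0.97.

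**Step 4: can 23 people estimate a share?** Work on the percentage-point scale.
- Sampling variance of one person's difference: 10⁴·(0.95·0.05/300 + 0.96·0.04/300) = 2.86.
- Simulated random-effects meta-regression, true share 50%, true effect SD 1 point: the estimated total effect variance is zero in about 19–20% of trials, which leaves the share undefined. In the other trials the central 95% of estimates runs from about −35% to 100%.
- At a true effect SD of 2 points it runs from about 3% to 100%.

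**The case against.** The strongest reply is that the Secondary analysis itself restates the question as the extent to which personal characteristics moderate the music effect, and presents the work as exploratory. Moderation is normally reported as an interaction with its interval, which is what is planned. Neither section mentions a variance share. This has force. The Objectives and the Secondary analysis can be read as asking different things, and the milder reading removes the mismatch. It does not remove the interval problem, which affects moderation estimates just as much.

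Some stronger readings are tempting, and the protocol does not support them:
- A reader might infer that interaction coefficients are the only output for question 2. Stratified descriptives are planned as well, although they do not separate explained from unexplained differences either.
- A reader might infer that the plan will present modifiers as explaining 100% of the differences. That figure is implied only on the log-odds scale and is nowhere reported or claimed. On the risk-difference scale, which the Estimand section uses, effects also vary through the random intercept. That variation reflects baseline accuracy, not unexplained response to music.
- A reader might expect someone to regress the separate per-person estimates on the modifiers and report a misleading R-squared. No such analysis is planned.

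It is also fair to object that an explained share is close to uninformative with 23 people. Step 4 of the working confirms this, and the fix is limited accordingly.

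**Conclusion.** The point stands in limited form. The planned model cannot show how much of the between-person difference in the music effect the modifiers explain, because on the log-odds scale it fixes the unexplained part at zero. This follows from Eq. (4) and the interaction step, and needs no assumed figure.

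The narrow intervals do depend on unexplained differences being present. At an unexplained SD of 0.2, close to the planned average effect of 0.234, the error rate rises modestly, from 5% to about 8%. At 0.5 it reaches roughly 22–27%. With no unexplained differences the planned intervals are sound. These sizes assume a binary modifier split 11/12 and the protocol's own accuracy rates and response counts.

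One might conclude that question 2 has no answer at all, or that a reliable explained share is within reach. Neither follows: the interactions and descriptives do inform moderation, and 23 participants cannot support a precise share. The point concerns a secondary question and leaves the primary population-level analysis as it is.

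**What to change.** In the effect-modifier model for question 2, add a participant-specific music effect s_i ~ N(0, σ_s²) and state its prior, which will carry weight with 23 people. Fit the model without and with the modifiers. Report σ_s with its 95% credible interval from both fits, next to the interaction coefficients. Give any explained share as a description only, and say that it is not estimable when σ_s without modifiers cannot be told apart from zero.

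If the team does not want this, reword secondary question 2 in the Objectives to match the Secondary analysis: whether the named modifiers moderate the music effect. Rewording alone settles the mismatch between the two sections but leaves the interval problem in place.

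The cost is one or two extra fits per modifier model on data already being collected, and wider interaction intervals: by factors of about 1.12, 1.25 and 1.61 at the three assumed values of σ_s. Conclusions about who benefits will be more cautious.
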